### Objective

The primary objective of this study is to determine if topical chlorhexidine 0.2% in combination with topical natamycin 5% is superior to topical natamycin 5% alone for treating fungal keratitis, in terms of vision at three months. The secondary objectives are: (1) to determine whether there is a difference between combination chlorhexidine 0.2% and natamycin 5% therapy and natamycin 5% alone for secondary clinical outcomes: infiltrate/scar size, time to re-epithelialisation, positive re-culture rates at one week; and (2) to investigate the effect of the alternative treatments on the Quality of Life of participants.

This trial is a response to the expressed need from both clinicians and patients for a readily available and affordable treatment strategy for fungal keratitis that can improve the likelihood of a good outcome. Our recent work in Uganda has shown promise for chlorhexidine 0.2% as an adjunctive therapy
^
19
^. If chlorhexidine 0.2% eye drops, which are very cheap and easy to prepare (by simple aqueous dilution), in combination with natamycin, are found to be superior to natamycin alone, then this offers a realistic, contextually relevant and sustainable solution for this aspect of the complex problem of fungal keratitis. Therefore, a full-scale trial investigating chlorhexidine 0.2% as adjunctive therapy is warranted to provide the evidence for its use.

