### Outcome assessments

Participants will undergo reassessment at various intervals following enrolment, as outlined in
Table 3. Examinations will be conducted similarly to the baseline assessment. Adherence to treatment and symptoms, including side effects, will be queried and recorded at each follow-up. Trial medication adherence will be monitored by weighing eye drop bottles at specified follow-ups, with resupply provided as necessary. Visual acuity will be measured at each visit, with BSCVA assessed at the three-month follow-up (primary outcome measure). Quality of life questionnaires will be repeated at the final three-month follow-up. Slit-lamp examination and corneal photography will be performed at each visit. In vivo confocal microscopy will be repeated at specified intervals to assess fungal hyphae resolution. If the ulcer has not healed at the one-week follow-up, re-scraping for repeat culture will be conducted. Appointment cards will be provided for follow-ups, and transport costs will be covered for outpatient participants.

**Table 3. T3:** Baseline and follow-up assessment components.

Assessment Item	Baseline	Day 2	Day 7	Day 14	Day 21	Day 60	Day 90
History / Baseline questionnaire	X						
Check treatment adherence		X	X	X	X	X	X
Check for side effects		X	X	X	X	X	X
Visual Acuity – Presenting	X	X	X	X	X	X	X
Visual Acuity – BSCVA	X						X
Contrast Sensitivity	X						X
Slit-lamp Examination	X	X	X	X	X	X	X
Cornea Photography	X	X	X	X	X	X	X
*In vivo* confocal microscopy	X		X	X	X		
Cornea samples (Microbiology/PCR)	X		X				
Quality of Life Tools	X						X

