### Analysis plan

An intention-to-treat (ITT) approach will be used, analyzing all data based on the assigned randomisation group, regardless of adherence to the treatment protocol. Analyses will follow CONSORT guidelines for non-inferiority trials
^
35
^, and a flowchart will summarize recruitment, randomisation, and follow-up by treatment arm. Baseline characteristics will also be summarized. Details of the SPIRIT checklist are provided as Extended Data and available online (see Data Availability Statement). 

**
*Primary outcome analysis – unadjusted*
**

The primary outcome (BSCVA at 3 months) will be analyzed using linear regression, including baseline BSCVA and treatment arm as covariates. Mixed fungal and bacterial infections identified at baseline will be excluded from the primary analysis. We will use our alpha of 0.0492 to test the null hypotheses at 0.0492 significance. Significance will be assessed using a two-tailed test at 0.0492 level for assessing superiority.

**
*Primary outcome analysis – adjusted*
**

If baseline covariate imbalances occur between treatment arms, adjusted analyses will be conducted to ensure treatment effects are not confounded by these differences. This is particularly important if natamycin + chlorhexidine has a better outcome than natamycin, as the adjusted treatment effects may account for this observed imbalance whilst the unadjusted analyses may not. Sensitivity analyses will allow us to show that any observed positive treatment effect is not solely explained by imbalances at baseline in any of the covariates.

**
*Secondary analyses of the primary outcome*
**

- Per-Protocol Analysis: Re-analysis will be conducted excluding participants with significant deviations, poor adherence (<50%), or mixed/non-fungal infections. 

- Mixed Infections: Secondary analyses will include mixed infections using the same methodology as the primary analysis. 

- Sensitivity Analyses: Missing data will be addressed through multiple imputation or non-random missing data models if necessary. Additional sensitivity analyses will assess outcomes in subgroups such as those with severe vision loss, corneal perforation, or therapeutic keratoplasty. 

**
*Analysis of other determinants for success*
**

Logistic regression models will identify factors associated with poor outcomes (BSCVA >1.0 logMAR), adjusting for trial arm. Multivariate models will refine predictors based on likelihood ratio tests. 

**
*Secondary outcome analysis*
**

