Time to full epithelial healing (slit lamp examination by ophthalmic clinician)	The time to re-epithelialization will be calculated as the midpoint between the last review showing an epithelial defect (ED) and the subsequent review where no ED is observed. Fluorescein staining covering an area smaller than 0.5 mm will be considered indicative of a resolved ED, given the challenge of distinguishing smaller defects from pooling in healed areas. Time-to-healing analysis will utilize Cox proportional hazards regression, with treatment group as the primary predictor and baseline ED size (geometric mean in mm) included as a covariate. Survival curves for treatment groups will be plotted using Kaplan-Meier analysis up to the three-month endpoint. The proportional hazards assumption will be tested by stratifying baseline ED size into quartiles. If this assumption is not met, stratified results will be reported. Treatment failure (defined as an ED larger than 0.5 mm at the three-month review) will be compared between groups using Fisher’s exact test.
Rate of healing	The rate of ulcer size reduction will be evaluated by measuring changes in ED size over time intervals (1 week to 3 weeks, and 3 weeks to 3 months) and dividing by the number of days, producing a rate (mm/day). This will be analyzed using Cox regression.
Microbiological cure	For patients with persistent corneal ulcers (defined by ED presence) at day 7, a repeat corneal scrape and microbiological tests will be conducted. Microbiological cure at day 7 will be defined as the absence of growth on culture. Cure rates will be compared between treatment arms using logistic regression, adjusting for organism type (e.g., *Aspergillus spp.*, *Fusarium spp.*, or other).
Ulcer depth at 1 week and 3 weeks (slit lamp examination by ophthalmic clinician).	Depth of corneal ulcers (expressed as a percentage of healthy cornea thickness) will be compared between treatment groups at one week and three weeks. This analysis will adjust for baseline ulcer depth using linear regression.
Hypopyon height at 1 and 3 weeks, (slit lamp examination by ophthalmic clinician)	Hypopyon height (in mm) at one and three weeks will be compared between groups, adjusting for baseline height using linear regression.

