Key eligibility criteria	1. Acute MK characterised by: • Corneal epithelial ulceration >1mm diameter • Corneal stromal infiltrate • Acute inflammation: e.g. conjunctival injection, anterior chamber inflammatory cells, hypopyon. 2. Filamentous fungal hyphae visualised on smear microscopy and/or *in vivo* confocal microscopy. 3. Agree to be randomised to either treatment arm and able to give informed consent 4. Agree to be followed up at 2 days, 1 week, 2 weeks, 3 weeks, 2 months and 3 months 5. Adults (18 years and older)
Study type	Randomised controlled trial
Date of first enrolment	12 May 2021
Target sample size	358
Recruitment status	Recruiting
Primary outcome(s)	Best Spectacle Corrected Visual Acuity (BSCVA) at 3 months by a trial certified optometrist
Key secondary outcomes	1. Time to full epithelial healing (slit lamp examination by ophthalmic clinician). 2. Pin-hole visual acuity in logMAR at 3 months, trial-certified optometrist 3. Scar/infiltrate size at 1 week, 3 weeks and 3 months (slit lamp examination by ophthalmic clinician). 4. Ulcer depth at 1 week and 3 weeks (slit lamp examination by ophthalmic clinician). 5. Hypopyon height at 1 and 3 weeks, (slit lamp examination by ophthalmic clinician). 6. Perforation and/or TPK by three months (slit lamp examination by ophthalmic clinician). 7. Positive culture rate at 1 week 8. Ocular adverse effects at each follow up visit (Day 2, Day 7, Day 14, 3 weeks, 2 months, 3 months), slit lamp examination by ophthalmic clinician. 9. Quality of life (QoL) assessed using: EQ-5D, WHO/PBD-VF20, WHOQOL-BREF (comparison between baseline and QoL measures at 3 months) 10. Cost-effectiveness analysis, using EQ-5D data from 3 months and direct cost data. 11. Drug adherence at each follow up visit (Day 2, Day 7, Day 14, 3 weeks, 2 months, 3 months) whilst the patient is using study medications.

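### Day-7 microbiological cure has a value only for eyes that still have an epithelial defect, so the comparison of arms conditions on a result of treatment and is not a randomised one

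*Protocol article*

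**What the plan says.** All references are to the protocol article.

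- **Who is re-cultured.** Table 4 (microbiological cure): "For patients with persistent corneal ulcers (defined by ED presence) at day 7, a repeat corneal scrape and microbiological tests will be conducted". The section on outcome assessments agrees: "If the ulcer has not healed at the one-week follow-up, re-scraping for repeat culture will be conducted".
- **What counts as cure.** "Microbiological cure at day 7 will be defined as the absence of growth on culture".
- **How arms are compared.** "Cure rates will be compared between treatment arms using logistic regression, adjusting for organism type".
- **General principle.** The analysis plan states an intention-to-treat approach, "analyzing all data based on the assigned randomisation group, regardless of adherence to the treatment protocol".
- **Where the outcome is named.** The secondary objective lists "positive re-culture rates at one week" next to time to re-epithelialisation. The registration summary in Table 5 lists "Positive culture rate at 1 week".
- **When a defect counts as healed.** In the healing-time row of Table 4: "Fluorescein staining covering an area smaller than 0.5 mm will be considered indicative of a resolved ED".

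The article does not say how an eye that has closed by day 7 is scored for microbiological cure.

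**The concern.** The article fixes three things: the sampling rule, the definition of cure and the model. Together they leave a closed eye without a culture and therefore without a value. The logistic regression then runs on open ulcers only.

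Whether an ulcer is still open at day 7 is not a baseline characteristic. Re-epithelialisation is itself a secondary outcome of this trial, and the introduction reports that healing speed differed by treatment in the earlier Nepal trial (39% slower on chlorhexidine than on natamycin). Restricting one outcome to participants selected by another that treatment can change removes the protection of randomisation. The eyes left in the two arms need not be comparable, and adjusting for organism type does not repair that.

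If the combination closes more ulcers in the first week, and closed eyes are mostly clear of culturable fungus, its early successes leave the denominator in greater number than those of the control arm. Its cure rate among the remaining eyes then understates its effect. What is at stake is the interpretation of one named secondary outcome.

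**Working it through.** **The plan's own figure.** The article gives no sample size or expected rate for day-7 culture. Its only calculation is for the primary outcome, and it reproduces: 2 × [(z for two-sided 0.0492 + z for 80% power) × 0.62 / 0.2]² = 151.6, so 152 per arm and 304 in total; 304 / 0.85 = 357.6, so 358. Nothing below alters it.

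**Inputs for the illustration.** From the article: 358 participants, 1:1, so 179 per arm. Assumed, because the article gives no figures: culture positivity at day 7 among all eyes (P), the share closed by day 7 (h), all 179 seen at day 7, no covariate adjustment, and closed eyes culture-negative (varied below). Power is the normal approximation for two proportions at two-sided 5%.

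**Formula.** If closed eyes are all negative, positivity among open eyes is P / (1 − h), with 179 × (1 − h) eyes per arm. Odds ratios are for a positive culture, combination v natamycin.

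**True benefit, P = 40% natamycin v 30% combination**

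| Closed by day 7 | Positivity among open eyes | OR | Power |
|---|---|---|---|
| none (all eyes) | 40.0% v 30.0% | 0.64 | 51% |
| 15% v 15% | 0.40/0.85 = 47.1% v 0.30/0.85 = 35.3% | 0.61 | 56% |
| 5% v 10% | 0.40/0.95 = 42.1% v 0.30/0.90 = 33.3% | 0.69 | 38% |
| 15% v 30% | 0.40/0.85 = 47.1% v 0.30/0.70 = 42.9% | 0.84 | 11% |
| 20% v 40% | 0.40/0.80 = 50.0% v 0.30/0.60 = 50.0% | 1.00 | effect gone |

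The second row shows that equal closure loses no benefit.

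**Gap needed to lose the effect.** Setting 0.40/(1 − h₁) = 0.30/(1 − h₂) gives h₂ = 1 − 0.75(1 − h₁). At h₁ = 5% this is h₂ = 28.75%; at 10%, 32.5%; at 20%, 40%. Repeating this for a 10-point benefit with control cure of 40% to 60% and control closure of 2% to 20% gives required gaps from 13 points (20% v 33.3%) to about 24 points (2% v 26.5%).

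**No true difference, P = 36% in both arms.** At 15% v 30% closed: 0.36/0.85 = 42.4% v 0.36/0.70 = 51.4%, OR 1.44, rejected about 33% of the time. At 5% v 10%: 0.36/0.95 = 37.9% v 0.36/0.90 = 40.0%, OR 1.09, rejected about 7% of the time.

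**If some closed eyes are positive.** With a share q of closed eyes negative, positivity among open eyes is [P − (1 − q)h] / (1 − h). For 40% v 30% and 15% v 30% closed, q = 0.95 gives 46.2% v 40.7%, OR 0.80. With q = 0.60 it gives 40.0% v 25.7%, OR 0.52, which exaggerates the benefit. The direction of the bias therefore depends on q being high.

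**The case against.** **The exclusion is implied, not stated.** The article never says that closed eyes leave the regression, and a fuller plan might score them as cured. This stands as a limit on wording. It does not remove the point: the published definition rests on a culture that closed eyes do not have, and the general intention-to-treat sentence gives them no value.

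**The larger effects rest on assumed closure rates.** This stands. The article describes slow antifungal response and therapy often lasting 4–6 weeks, so few ulcers may have closed by day 7. A reader might infer that a real benefit would probably vanish or reverse in this trial. The article has no figures to support that. The no-difference case is also a demanding pairing, since it doubles closure in one arm while leaving overall positivity equal.

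**The tables might seem to contradict each other.** Table 5 names a one-week culture rate without mentioning open ulcers. That is a short registry label for the outcome detailed in Table 4, not a contradiction.

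**The Nepal result might seem to show the bias at work.** There, healing differed but day-7 re-culture did not differ significantly (P=0.233). The article does not give the denominator, so this cannot be concluded.

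**The remedy changes the outcome.** Scoring closed eyes as not culture-positive makes a composite of closure and culture, and closure is already analysed elsewhere. This is fair, and a reason to report the components. Whether fungus persists in open ulcers is a legitimate descriptive question, but the open-ulcer analysis does not give a randomised estimate of treatment effect.

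**Conclusion.** The point holds in a limited form. As specified, the day-7 comparison conditions on a post-randomisation variable that treatment can change, so its odds ratio is not a randomised comparison. That conclusion needs no assumed rates.

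Bias against the faster-healing arm follows only if closure differs between arms and closed eyes are mostly culture-negative. Under the assumed rates a modest closure gap costs little on the odds ratio scale, while a doubling from 15% to 30% takes away most of the effect. Complete loss or reversal is possible, but needs a gap of roughly 13 to 24 points by day 7 in the range examined. The actual size in this trial cannot be derived from the article. The issue is confined to one secondary outcome.

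**What to change.** In the microbiological cure row of Table 4, or in the analysis plan:

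1. Compare the proportion culture-positive at day 7 among all randomised eyes seen at day 7, by assigned arm. Count an eye with no epithelial defect, and hence no scrape, as not culture-positive. State the closure threshold used. An open eye without a culture result is missing, not negative.
2. Report by arm the numbers closed, culture-negative, culture-positive and missing.
3. Keep the open-ulcer comparison, labelled as descriptive.

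The cost is a few sentences and one small table. No new procedure is needed, because the slit-lamp examination at day 7 already records the defect. The downside is that closed eyes are assumed, not shown, to be culture-negative, and the outcome becomes a composite of closure and culture. The confocal scan scheduled for day 7 in Table 3 allows a partial check of that assumption.

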### Baseline assessment

The comprehensive baseline assessment is delineated in
Table 2. This encompasses clinical examination, corneal photography, in vivo confocal microscopy, and the procurement of microbiology samples. Additionally, participants will complete quality of life questionnaires, namely EQ-5D,24 WHO/PBD-VF20,25 and WHOQOL-BREF,26 with scoring details provided in
Table 2.

**Table 2. T2:** Baseline assessment. Assessment performed at baseline with details of how they are made.

Assessment	Details
Visual Acuity	Visual acuity, including Presenting, Pin-Hole, and Best Spectacle Corrected Visual Acuity (BSCVA), will be assessed using an ETDRS Tumbling-E logMAR 3m chart (Precision Vision, USA) mounted on an ESC 2000 ETDRS LED Cabinet (Precision Vision, USA). A trial-certified optometrist will perform these assessments separately for each eye.
Contrast Sensitivity	Contrast sensitivity will be evaluated using the Peek Contrast Sensitivity smartphone application, installed on an Android device (Sony Xperia Z3 Compact smartphone, Sony, Japan) ^ 24 ^.
Clinical Photographs	Photographs of both corneas will be taken using a Nikon D7500 camera equipped with an AF-S Micro Nikkor 105mm lens and SB-200 flash units (Nikon, Japan). A standardized protocol will be followed to ensure consistency in images across time points. Magnification will be standardized, enabling measurements of epithelial defects and stromal infiltrates.
Slit-lamp examination	A slit-lamp biomicroscope will be used to examine the anterior segment of both eyes, conducted by an ophthalmic clinician experienced in microbial keratitis management. Particular focus will be given to: 1. Eyelids: trichiasis, lagophthalmos, facial weakness, Bell’s reflex. 2. Suppuration. 3. Conjunctival inflammation. 4. Corneal sensation. 5. Corneal epithelial defects (including dimensions and ulcer depth). 6. Corneal inflammatory infiltrate characteristics: depth, size, profile, color, edge pattern, texture, satellites. 7. Anterior chamber inflammation: inflammatory cells, hypopyon, endothelial plaque. 8. Relative afferent pupillary defect.

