Secondary outcomes listed in
Table 4 will be analyzed using regression models appropriate for the data type, adjusting for any baseline imbalances. 

**Table 4. T4:** Secondary Outcome Measures that will be investigated as part of the trial, together with analysis details.

Secondary outcome measure	Details
Three-week BSCVA	We will analyze the secondary outcome of three-week Best Spectacle-Corrected Visual Acuity (BSCVA) in logMAR using the same methodology applied to the primary analysis of the primary outcome. The three-week BSCVA assessment will include values recorded between 18 days and 5 weeks, with the closest value to 3 weeks being selected.
Presenting VA by Peek	The presenting visual acuity (VA) assessed using Peek Acuity, with and without pinhole, will also be analyzed as a secondary outcome at three months. This measure will be particularly relevant if reliable BSCVA readings cannot be obtained at three months (e.g., if patients do not attend the clinic and at-home visual acuity testing is required). This analysis will follow the same approach as the primary analysis of the primary outcome. A sensitivity analysis, incorporating data from participants lost to follow-up, will use the most recent recorded observation of this variable.
Scar/infiltrate size at 1 week, 3 weeks and 3 months by slit lamp examination.	For scar or infiltrate dimensions, the geometric mean of the two principal axes (in mm) will serve as the outcome variable at one week, three weeks, and three months. The scar size, observed via slit lamp, will be compared between treatment groups at each time point using linear regression. This will include treatment arm and baseline infiltrate/scar size as predefined covariates, controlling for baseline differences.

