Perforation and/or TPK and/or conjunctival advancement by three months (slit lamp examination by ophthalmic clinician)	The number of patients requiring perforation repair via Therapeutic Penetrating Keratoplasty (TPK), conjunctival advancement, or experiencing perforation itself by three months will be reported using confidence intervals and descriptive statistics. Since the study is not powered to detect significant differences in perforation or TPK rates, exploratory logistic regression analyses will estimate odds ratios for these outcomes between groups.
Loss of Eye	The proportion of patients requiring surgical removal of the eye (evisceration or enucleation) during follow-up will be described with confidence intervals. Logistic regression will explore treatment arm differences and associated risk factors.
Ocular adverse effects, slit lamp examination by ophthalmic clinician.	TThe occurrence of adverse events will be assessed by Fisher’s exact test. Poisson regression will compare adverse event rates, accounting for multiple events per participant.
Quality of life assessed using: EQ-5D, WHO/PBD-VF20, WHOQOL-BREF	QoL outcomes will be assessed using tools tailored to specific interests ^ 38 ^. Disease-related QoL will be evaluated with the WHO/PBD-VF20 (20-item Vision Function Questionnaire), which assesses the impact of visual impairment on mental well-being, dependency, and social functioning. For general health-related QoL, tools include the EQ-5D questionnaire, EQ-Visual Analogue Scale, and the WHOQOL-BREF. The EQ-5D provides standardized health outcome measures, while the WHOQOL-BREF evaluates four domains: Physical Health, Psychological Health, Social Relationships, and Environment. Scoring details for these tools are provided in Table 2. Comparisons of QoL scores between treatment groups will estimate the effects of chlorhexidine and natamycin. Adjustments will be made for variables like age, sex, socio-economic status, and recent health problems. Logistic, linear, and ordinal logistic regression methods will be employed depending on whether the outcome variables are binary, continuous, or ordered categorical. Mean scores and mean differences in QoL subscales and domains will be compared using t-tests and linear regression.

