Cost effectiveness analysis, using EQ-5D data from 3 months and direct cost data	Direct costs incurred by patients will be collected at the three-month follow-up, with economic costs estimated from EQ-5D data collected at baseline and follow-up. Mean direct costs will be compared between treatment arms using t-tests. Changes in EQ-5D scores from baseline to follow-up will also be analyzed similarly.
Drug adherence	The rate of adherence to treatment protocols will be evaluated using descriptive statistics, comparing compliance between the two treatment arms.

**
*Interim analysis*
**

An independent statistician will conduct an interim analysis after 1/3 of participants complete follow-up. 

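### The quality-of-life and EQ-5D comparisons do not pre-specify the baseline score as a covariate, although every tool is completed at baseline, and so give up precision

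*Protocol article*

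**What the plan says.** The effect of treatment on quality of life is one of the two secondary objectives (Objective). The three tools are completed at baseline (Baseline assessment, Table 2), and "Quality of life questionnaires will be repeated at the final three-month follow-up" (Outcome assessments; Table 3 agrees).

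The analysis is spread over several places:

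- Table 4, quality-of-life row: "Adjustments will be made for variables like age, sex, socio-economic status, and recent health problems". The same row adds: "Mean scores and mean differences in QoL subscales and domains will be compared using t-tests and linear regression".
- Table 4, cost-effectiveness row: "Mean direct costs will be compared between treatment arms using t-tests", and then "Changes in EQ-5D scores from baseline to follow-up will also be analyzed similarly". Read together, EQ-5D change is compared between arms by t-test.
- General rule ahead of Table 4: the outcomes in "Table 4 will be analyzed using regression models appropriate for the data type, adjusting for any baseline imbalances".
- Table 5 lists quality of life as a key secondary outcome, described as a "comparison between baseline and QoL measures at 3 months".

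The baseline score is not named as a covariate in any of these.

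**The concern.** A three-month score is usually related to the same patient's baseline score. A model that includes the baseline score removes that part of the variation, whereas a t-test on the three-month score leaves it in the error. A t-test on change removes it only by subtraction. With equal SDs, subtraction makes the comparison noisier than ignoring baseline altogether when the correlation is below 0.5.

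The plan follows the better practice elsewhere. BSCVA, scar/infiltrate size, ulcer depth and hypopyon height each have their own baseline value as a stated covariate, and baseline epithelial defect size enters the Cox model for healing. The article gives no reason for treating quality of life differently. At stake are the width of the confidence intervals and the power for a stated secondary objective, using data that the trial already collects.

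**Working it through.** **The plan's own figure.** No sample size or power is given for quality of life. The only size in the plan is for BSCVA: difference 0.2, SD 0.62, two-sided alpha 0.0492, power 80%. Per arm, 2 × 0.62² × (1.967 + 0.842)² / 0.2² = 151.6, rounded up to 152, so 304 in total (power 80.1%). Then 304 / 0.85 = 357.6, giving 358. Both figures reproduce, and this point does not touch them. I use 152 per arm below as the number with three-month data.

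**Assumptions.** The documents give no baseline to three-month correlation r for any tool, so r is assumed, from 0.2 to 0.7. The SD is first taken as equal at both visits.

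**Formulas.** Variance of the arm difference relative to a t-test on the three-month score:

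- three-month t-test: 1
- change-score t-test: 1 + 1 − 2r = 2(1 − r)
- linear model with baseline score: 1 − r²
- baseline-adjusted against change score: (1 − r²) / [2(1 − r)] = (1 + r) / 2

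| r (assumed) | Change score, relative variance | Baseline-adjusted, relative to three-month t-test | Baseline-adjusted, relative to change t-test | Equivalent extra patients, vs three-month / vs change |
|---|---|---|---|---|
| 0.2 | 1.60 | 0.96 | 0.60 | 4% / 67% |
| 0.3 | 1.40 | 0.91 | 0.65 | 10% / 54% |
| 0.5 | 1.00 | 0.75 | 0.75 | 33% / 33% |
| 0.7 | 0.60 | 0.51 | 0.85 | 96% / 18% |

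The two gains run in opposite directions. A low correlation makes the change score costly and the three-month t-test nearly harmless; a high one does the reverse.

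**Power.** Take alpha 0.05 (assumed for these outcomes) and 152 per arm. The effect that gives the three-month t-test 80% power is (1.960 + 0.842) × √(2/152) = 0.32 SD. For that effect, at r = 0.2, 0.3, 0.5 and 0.7:

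- baseline-adjusted: 82%, 84%, 90%, 98%
- change-score t-test: 60%, 66%, 80%, 95%

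**If the SDs differ.** Let k be the baseline SD divided by the three-month SD. The change score then has relative variance 1 + k² − 2rk. Subtracting 1 − r² leaves (k − r)², which is never negative. So the adjusted model is at least as precise as the change score whatever the SDs. Only the size of the gain depends on k, and the 1 − r² comparison with the three-month t-test does not depend on k.

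**The case against.** The strongest reply is that the text does not rule the baseline score out. The covariate list is given by example, and the rule ahead of Table 4 would bring in a baseline score that turned out to be imbalanced. The article is also a condensed protocol, and a full covariate list for a secondary outcome can properly sit in an analysis plan that is not shown. This stands in part: it would be wrong to say that the plan forbids or never allows baseline adjustment. It does not remove the point, because the article goes beyond silence. It states t-tests, names the kind of covariates meant, and states a change-score t-test for EQ-5D. Adjustment that depends on an observed imbalance is not a pre-specified covariate and brings no precision gain when the arms are balanced.

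A reader might also infer that baseline data are ignored throughout. The documents do not support that. EQ-5D change uses baseline by subtraction, Table 5 describes a comparison with baseline, and the quality-of-life row does not give a time point or say whether its mean differences are between arms or from baseline. That the t-tests are on three-month scores is a reading, not a statement.

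Three more limits are fair. The benchmark here is an unadjusted t-test; the plan also has a covariate-adjusted regression, and the gain over that cannot be computed from the documents. The 1 − r² formula does not carry over to the logistic and ordinal models that the row also allows, where adjustment changes the odds ratio being estimated. And a reader might suspect that recent health problems is measured after randomisation; the article does not say when it is asked, so this is no more than a reason to specify baseline values.

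**Conclusion.** The point holds as one of efficiency. For continuous quality-of-life scores, including EQ-5D, the stated t-tests are no better than a linear model with the baseline score, and are worse at any correlation between 0 and 1 when the SDs are equal. The plan already uses the better method for its primary outcome and several secondary ones.

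The size is uncertain because it rests on an assumed correlation. Over 0.2 to 0.7, the reduction in variance is 4% to 49% against a three-month t-test and, with equal SDs, 40% to 15% against a change-score t-test. A headline of a third more patients belongs to a correlation of exactly 0.5 and should not be quoted as the loss. If baseline, taken during acute disease, predicts three-month quality of life only weakly (0.2 to 0.3), the loss against a three-month t-test is 4% to 9% of variance, and the change-score test is the one that suffers.

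Randomisation keeps all of these comparisons unbiased, and the primary analysis and sample size are unaffected. The change is worth making because it uses data already collected.

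**What to change.** In the quality-of-life row of Table 4, state that for each continuous score, including EQ-5D, the main between-arm comparison is a linear regression of the three-month score on treatment arm and the baseline score of the same tool, in place of the t-tests. Centre may be added, because each centre has its own randomisation sequence. List any further covariates in full and restrict them to values recorded at baseline.

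In the cost-effectiveness row, take the EQ-5D comparison from the same model. Change from baseline can still be described by arm; with baseline in the model, the arm effect is the same whether the outcome is the three-month score or the change, so the Table 5 description is respected.

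The cost is a sentence or two of wording and no new data. Two small items come with it: a rule for patients with a missing baseline questionnaire, and, where a binary or ordinal model is kept, a statement that its odds ratio is conditional on the covariates. If the full analysis plan already contains this model, the article's wording only needs to be brought into line.
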